## Abstract

**Background:**

About 5%–15% of acute coronary syndrome (ACS) patients undergoing stent implantation have concomitant atrial fibrillation and need both antiplatelet and anticoagulant therapies. The optimal antithrombotic regimen remains uncertain in this scenario.

**Hypothesis:**

A multicenter randomized controlled trial (OPtimal management of anTIthroMbotic Agents [OPTIMA]‐4) is designed to test the hypothesis that, for ACS patients with concomitant nonvalvular atrial fibrillation (NVAF) and having low‐to‐moderate risk of bleeding, clopidogrel is comparable in efficacy but superior in safety compared to ticagrelor while being used in combination with dabigatran after new‐generation drug‐eluting stent (DES) implantation.

**Methods:**

ACS patients who have low‐to‐moderate risk of bleeding (e.g., HAS‐BLED score ≤ 2) and require anticoagulation therapy (CHA_2_DS_2_‐VASc score ≥ 2) will be recruited after implantation of new‐generation DES. A total of 1472 eligible patients will be randomly assigned to receive a 12‐month dual antithrombotic treatment of either clopidogrel 75 mg daily or ticagrelor 90 mg twice daily in combination with dabigatran 110 mg twice daily. Participants will be followed up for 12 months after randomization. The primary efficacy endpoint is a composite of cardiovascular death, myocardial infarction, unplanned revascularization, ischemic stroke, and systemic thromboembolism. The primary safety endpoint is set as major bleeding or clinically relevant nonmajor bleeding defined by the International Society of Thrombosis and Hemostasis. The enrollment and follow‐up have been launched.

**Results:**

The first enrollment occurred on March 12, 2018. The recruitment is anticipated to be completed before December 31, 2024.

**Conclusions:**

The OPTIMA‐4 trial offers an opportunity to assess the optimal dual antithrombotic regimen in ACS patients with concomitant NVAF after the implantation of new‐generation DES.

## INTRODUCTION

1

Dual antiplatelet therapy (DAPT) with aspirin and adenosine diphosphate (ADP) antagonist has been recommended for patients after drug‐eluting stent (DES) implantation to prevent stent thrombosis (recommendation level: IA),^1^ and oral anticoagulants (OAC) is recommended for atrial fibrillation (AF) patients with CHA_2_DS_2_‐VASc score ≥ 2 to prevent ischemic stroke.^2^ Thus, for patients undergoing percutaneous coronary intervention (PCI) with concomitant AF, triple antithrombotic therapy (TATT) including both DAPT and OAC would be indicated.^3^ However, previous studies have reported that TATT based on warfarin or new oral anticoagulants (NOAC) significantly increased the bleeding incidence compared with dual antithrombotic therapy (DATT).^4^, ^5^

The new‐generation DES with better biocompatibility or biodegradable polymers or non‐polymer has been widely used in clinical practice. Compared with the first‐generation DES, the new‐generation DES is associated with faster endothelialization and lower incidence of stent thrombosis and is therefore less dependent on DAPT.^6^ In the era of new‐generation DES, current guidelines have recommended a shortened duration (1 week to 1 month) of TATT in acute coronary syndrome (ACS) patients with concomitant AF undergoing PCI.^2^, ^7^ Additionally, concerning about high bleeding risk prevailing, 12‐month DATT including a NOAC in preference to warfarin is recommended to be administered in ACS patients with concomitant AF after PCI^2^, ^7^ referring to several randomized controlled trials (RCTs), i.e., PIONEER AF‐PCI, RE‐DUAL PCI, AUGUSTUS, and ENTRUST‐AF PCI.^5^, ^8^, ^9^, ^10^ However, it has not been demonstrated which ADP antagonist (e.g., clopidogrel or ticagrelor) is optimal to be coadministered with NOAC. Furthermore, it is uncertain whether DATT is suitable for the same patients but with low to moderate risk of bleeding.

The Platelet Inhibition and Patient Outcomes (PLATO) trial has found that in ACS patients, ticagrelor significantly decreased cardiovascular death by 21.6% compared with clopidogrel while being used in combination with aspirin.^11^ Nevertheless, the ticagrelor arm increased major bleeding by 0.7% (4.5% vs. 3.8%, *p* = .03).^11^ Thus, there is a concern about the bleeding risk under the DATT of NOAC combined with the most potent antiplatelet agent ticagrelor. It is uncertain whether there is any difference between ticagrelor and clopidogrel while being coadministered with a NOAC in post‐PCI ACS patients with concomitant AF.

Our OPtimal management of anTIthroMbotic Agents (OPTIMA)‐4 trial is designed to test the hypothesis that, for ACS patients with concomitant nonvalvular atrial fibrillation (NVAF) and having low‐to‐moderate risk of bleeding, clopidogrel is comparable in efficacy but superior in safety compared to ticagrelor while being used in combination with dabigatran after new‐generation DES implantation.

## METHODS

2

### Study design

2.1

A multicenter, open‐label, randomized, controlled clinical trial (OPTIMA‐4) is designed. The study design is shown in Figure 1. The study complies with the Declaration of Helsinki as amended in Seoul, Korea (64th, 2013), and is to be performed in accordance with the International Conference on Harmonization “Good Clinical Practices.” Before participating in this study, patients should be informed about the objectives, rights, duties, possible risks, and benefits of the study in lay language, and written informed consent should be signed as required. Written informed consent for publication of their clinical details and/or clinical images should be obtained from the patient/parent/guardian/relative of the patient. Patients can be identified only by a unique identification code and randomization number to maintain their confidentiality. The investigators will report the progress of this study to the ethics committee annually until the study is completed. The study has been registered at Clinicaltrials.gov (identifier: NCT 03234114).

**Figure 1 clc24025-fig-0001:**
[figure not shown]
Flowchart of OPtimal management of anTIthroMbotic Agents‐4 trial. DES, drug‐eluting stent; PCI, percutaneous coronary intervention; R, randomization.

### Participant selection

2.2

The main inclusion criteria are ACS patients with concomitant nonvalvular AF, who underwent new‐generation DES implantation with CHA_2_DS_2_‐VASc score ≥ 2 and in an acceptable risk of bleeding (e.g., HAS‐BLED score ≤ 3). The detailed inclusion and exclusion criteria are listed in Table 1. A total of 1472 patients will be required and recruited at 66 medical centers in China (see Supporting Information: Appendix 2).

**Table 1 clc24025-tbl-0001:** Inclusion and exclusion criteria.

Inclusion criteria
≥18 years
ACS patients with concomitant paroxysmal, permanent, or persistent nonvalvular AF underwent new‐generation DES implantation
CHA_2_DS_2_‐VASc score ≥ 2
In an acceptable risk of bleeding at the discretion of researchers (e.g., HAS‐BLED score ≤ 3)
Consent to participate in the trial
Exclusion criteria
DES implanted in the left main coronary artery
Cardiogenic shock or Killip III–IV
STEMI patients with malignant arrhythmias or underwent electrodefibrillation or cardiopulmonary resuscitation or with cardiac mechanical complications (heart rupture, ventricular septal perforation, nipple muscle fracture, etc.)
History of gastrointestinal or intracranial hemorrhage; active bleeding, trauma, or major surgery within 1 month; suspected or diagnosed aortic dissection
Ischemic stroke with limb dysfunction or dysphasia
Known allergy or intolerance to the study medications: warfarin, clopidogrel, aspirin, dabigatran, ticagrelor, and heparin
Participating in other ongoing trials
Planned surgery in 12 months requiring to withdraw of the antiplatelet agents
Planned AF ablation or left atrial appendage occlusion in the next 12 months
Abnormal liver or kidney function (ALT > 3 ULN; estimated CrCl < 30 mL/min/1.73 m^2^ calculated by Cockcroft–Gault equation); diagnosed of liver cirrhosis
Hematological disease with bleeding tendency; hemoglobin < 100 g/L; platelet count < 100 × 10^9^ cells/L
Malignancies or life expectancy of less than 1 year
Pregnant (present, suspected, or planned) or lactating woman
Patients who are taking drugs which may interact with study agents, such as miconazole, ketoconazole, fluconazole, voriconazole, itraconazole, posaconazole, efinaconazole, and rifampicin
Patients with any other conditions that may not be suitable to participate in the trial at the discretion of the researchers

Abbreviations: ACS, acute coronary syndrome; AF, atrial fibrillation; ALT, alanine aminotransferase; CrCl, creatinine clearance; DES, drug‐eluting stent; STEMI, ST‐segment elevation myocardial infarction; ULN, upper limit of normal.

### Randomization

2.3

Within 120 h of the new‐generation DES implantation, eligible patients will be randomized in a 1:1 ratio to receive either clopidogrel 75 mg daily or ticagrelor 90 mg twice daily in combination with dabigatran 110 mg twice daily for 12 months. The randomization will be done by the investigators through a central 24 h computerized randomization system of REDCap,^12^ using a random permuted block design with block sizes of four. The system can be accessed using personalized login data. Treatment allocation will be revealed for the patients and attending physicians.

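### One fixed, published block size of four in an open-label trial: if blocks are formed within centre, about a third of allocations can be deduced in advance

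*Protocol article*

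**What the plan says.** Section 2.3 of the protocol article specifies that "eligible patients will be randomized in a 1:1 ratio", "using a random permuted block design with block sizes of four". No other block size is mentioned. On who operates the system, it says "The randomization will be done by the investigators through a central" round-the-clock REDCap service. After assignment, "Treatment allocation will be revealed for the patients and attending physicians". Section 2.1 describes "A multicenter, open‐label, randomized, controlled clinical trial".

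Section 2.2 has patients "recruited at 66 medical centers in China", 1472 in total. One inclusion criterion in Table 1 reads "In an acceptable risk of bleeding at the discretion of researchers", with a HAS-BLED cut-off given only as an example.

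The article names no stratification factor and does not say whether blocks are formed within centre or run along one list for the whole trial. A condensed article may leave that to the full protocol, so the silence is not a fault in itself. It does mean that both cases have to be worked through. The Data Availability statement shows that the article appeared before enrolment had finished.

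**The concern.** A central system hides the next assignment, but it does not stop staff deducing it. When every block has four places, two per arm, and past assignments are open, someone who has seen the earlier members of a block knows the last one, and sometimes the last two. Publishing the block size during recruitment removes the need to infer it.

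The room to act on such knowledge lies in the discretionary criterion, and that criterion concerns bleeding risk, which is what the Step 1 endpoint measures. The Introduction itself records a worry about bleeding with ticagrelor plus an oral anticoagulant. A physician who shares that worry and expects the next assignment to be ticagrelor could judge a borderline patient unsuitable.

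The ticagrelor arm would then hold fewer patients at high bleeding risk and look safer than it is. That shrinks the apparent advantage of clopidogrel in Step 1. Under section 2.9 the noninferiority test in Step 2 is not performed if Step 1 fails, so the loss could extend to the efficacy question. Blinded event review protects how events are classified, not who enters each arm.

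**Working it through.** The article gives no predictability figure to reproduce. The inputs are the block size of four and 1:1 ratio (section 2.3), and 1472 patients at 66 centres (section 2.2), which is 1472/66 = 22.3, about 22 per centre. Whether blocks run within centre is an assumption, taken both ways.

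**Case A: blocks within centre, earlier local allocations known.** There are six equally likely orders of two and two.

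- Place 1: nothing is known; best guess right 1/2.
- Place 2: the other arm has two of the three remaining places; right 2/3.
- Place 3: certain if the first two matched (probability 1/3), otherwise even; right 1/3 × 1 + 2/3 × 1/2 = 2/3.
- Place 4: always certain; right 1.

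Certain allocations per complete block: 1/3 + 1 = 4/3 of 4, or 33.3%. Best-guess accuracy: (1/2 + 2/3 + 2/3 + 1)/4 = 17/24 = 70.8%, against 50% for unpredictable allocation.

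A centre with 22 patients has five complete blocks and two patients of a sixth. Certain: 5 × 4/3 = 6.7 patients, and 6.7/22 = 30%. Correct guesses: 5 × 17/6 + 1/2 + 2/3 = 15.3, and 15.3/22 = 70%. Simulation of 4000 such centres gave 30.4% and 69.8%.

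**Case B: one list for all centres, each investigator seeing only the own centre.** Let a centre supply a share s of patients in random order. One of its allocations is certain only if both earlier members of one arm in that block came from the same centre. At place 3 this has probability s²/3, and at place 4 it is s². Averaged over four places: (s²/3 + s²)/4 = s²/3.

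| Centre's share | s²/3 | Simulated (200 runs of 1472) |
|---|---|---|
| 1/66 (equal centres) | 0.008% | 0.01% |
| 25% | 2.1% | 2.0% |
| 50% | 8.3% | 8.3% |

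These are upper limits, because they credit the investigator with knowing where each block starts. With 66 equal centres, guessing the locally under-represented arm was right 50.0% of the time.

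**Effect of varying the block size** (22 patients per centre, blocks within centre, a best guesser who knows which sizes are in use):

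| Block sizes | Certain | Best guess right |
|---|---|---|
| 4 only | 30.4% | 69.8% |
| 4 or 6 | 6.0% | 68.6% |
| 4, 6 or 8 | 2.3% | 67.3% |

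Varying the size removes nearly all the certainty but little of the guessing advantage, which comes from balancing within a centre at all.

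**Timing.** Randomization may take place at any time within 120 h of stenting. The first enrolment was on 12 March 2018 and recruitment was expected to finish before 31 December 2024, about 2486 days. With even accrual an average centre enrols 22.3/2486 × 5 = 0.045 patients in 120 h. Delaying a patient changes the within-centre assignment only if another patient is randomised there meanwhile, which would be rare. On a central list about 1472/2486 × 5 = 3 patients enter in that time across all centres, and a local observer does not see most of those assignments.

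**The case against.** The strongest answer is that the scheme may not be predictable at all. The system is central, no stratification by centre is mentioned, and on one list over 66 similar centres the local advantage is nil. That stands. A reader might infer from the block size alone that upcoming allocations are predictable, but the article supports this only under the condition in Case A.

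A reader might also infer that selection bias has occurred or that it would favour clopidogrel. The article contains no evidence of steering, and the plausible direction, keeping patients at high bleeding risk off ticagrelor, is conservative for the superiority claim. The risk is a missed Step 1, not a spurious one. No size of bias can be derived from the article.

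Two further links are weaker than they look. The 120 h window offers little room for reordering at the trial's accrual rate; declining to enrol is the more realistic route. And Table 1 assigns the bleeding judgement to researchers while section 2.3 has investigators randomise. That these are the same people is likely but not stated.

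Finally, section 2.9 already plans baseline comparisons between arms, so part of the check exists. What remains is that one known block size, in an open-label trial with discretionary eligibility, gives up protection that costs almost nothing to keep.

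**Conclusion.** The point holds conditionally, as a cheap improvement. The premises are all in the article: one block size, disclosed during enrolment, open allocations, randomisation by investigators and a discretionary bleeding criterion. The consequence depends on the unstated structure of the list. Within-centre blocks make about 30% of allocations certain at 22 patients per centre (one third in complete blocks) and about 70% guessable. A single central list brings certainty to about 0.01% with equal centres, rising to about 2% or 8% of a centre's own patients if it recruits a quarter or half of the trial. The within-centre figures assume that staff keep track of earlier local allocations, and the average of 22 per centre assumes equal recruitment.

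**What to change.** For patients still to be randomised, replace the fixed block of four with block sizes varying at random, for example 4, 6 and 8, and do not disclose the sizes to sites. Keep the stratification structure now in use. If the list is central, do not introduce within-centre blocks: that would raise local guessing accuracy from about 50% to about 67%. If blocks are already within centre, certain allocations fall from about 30% to about 2%, while best-guess accuracy falls only to about 67%.

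Add HAS-BLED to the planned between-arm baseline comparison, for the period under fixed blocks, as a check on steering. It can reveal steering only on what the score captures, so a null result is reassuring but not proof.

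The cost is a short amendment, a new allocation table in REDCap and a slightly larger chance imbalance between arms. If recruitment has already closed, the list change lapses and only the HAS-BLED comparison remains.

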### PCI procedure

2.4

PCI procedures will be performed by well‐experienced interventional cardiologists performing over 500 cases of PCI per year, and radial access should be chosen as a priority. Successful PCI is defined as thrombolysis in myocardial infarction flow grade 3 in the target vessel with less than 10% residual stenosis. New‐generation DES (with better biocompatibility or biodegradable polymers or non‐polymer demonstrated in Supporting Information: Appendix 3) is required to be implanted in OPTIMA‐4 trial.

### Combined medications

2.5

The low‐molecular‐weight heparin (LWMH) (100 IU/kg, injected subcutaneously every 12 h) is recommended for up to 7 days during the perioperative period. Dabigatran is required to be prescribed after randomization and discontinuation of the LWMH. A bolus of unfractionated heparin (UFH) (100 IU/kg) should be injected intravenously during the PCI procedure. The activated clotting time (ACT) should be monitored every 1 h and an extra UFH should be administered if the ACT is low than 300 s. The platelet glycoprotein IIb/IIIa receptor inhibitors, e.g., Tirofiban, are not recommended unless a heavy thrombus burden is shown in coronary angiography. Other antithrombotic agents, e.g., prasugrel or rivaroxaban, are not allowed to be administered during the study period. Proton pump inhibitors could be administered for patients with high risk of gastrointestinal bleeding. Other medications (e.g., statins, β‐blockers, angiotensin‐converting enzyme inhibitors, etc.) could be administered at the discretion of the attending physicians.

### Pharmacodynamic, pharmacokinetic, and pharmacogenomic studies

2.6

The pharmacodynamic, pharmacokinetic, and pharmacogenomic studies of the antithrombotic agents will be performed in qualified centers for consented participants. The pharmacodynamic study of the antiplatelet drugs will be performed by light transmission aggregometry (LTA). In detail, 2 mL venous blood will be separately collected into two 3.2% sodium citrate vacutainer tubes (Becton, Dickinson and Company) at 7:30 a.m. on the day of discharge. Then blood samples will be subjected to an LTA test within 2 h, as previously described.^13^ Samples will be centrifuged at 200*g* for 8 min to obtain platelet‐rich plasma (PRP). Platelet‐poor plasma (PPP) will be prepared by centrifuging the remaining blood at 2465*g* for 10 min. Platelet counts will be adjusted by adding PPP to the PRP to achieve a count of 250 × 10^9^/L. Both the ADP (final concentration 5 μmol/L) induced platelet aggregation (PL_ADP_) and the arachidonic acid (AA) (final concentration 1 mmol/L) induced platelet aggregation (PL_AA_) will be detected using the Chronolog Model 700 aggregometer (Chrono‐log Corporation). The pharmacokinetic study of dabigatran will be performed as follows. Venous blood (2 mL) will be collected into a 3.2% sodium citrate vacutainer tube (Becton, Dickinson and Company) at 0.5 h before the dosing after at least six doses. Samples will be centrifuged at 2500*g* for 15 min at 25°C within 1 h. After centrifugation, the upper plasma will be stored below −80°C, and the concentration of dabigatran will be detected by high‐performance liquid chromatography‐tandem mass spectrometry in the pharmaceutical department of Fujian Medical University Union Hospital.^14^ The pharmacogenomic studies of the antithrombotic agents will be performed as follows. Two milliliters of blood will be drawn into a BD Vacutainer tube (Becton, Dickinson and Company) containing 3.6 mg K2‐ethylenediaminetetraacetic acid and stored below −80°C. The following single‐nucleotide polymorphisms (SNPs) will be detected: (1) clopidogrel‐related SNPs: CYP2C19 (rs12248560, rs28399504, rs41291556, rs4244285, rs4986893, rs5633701, rs72552267, rs72558186)^15^, ^16^; (2) ticagrelor‐related SNPs: SLCO1B1 (rs113681054), OATP1B1 (rs4149056), CYP3A4 (rs62471956, rs56324128), UGT2B7 (rs61361928)^17^; and (3) dabigatran‐related SNP: ABCB1 (rs4148738, rs1045642), CES1 (rs8192935).^18^, ^19^

### Endpoints

2.7

The primary efficacy endpoint of the OPTIMA‐4 trial is a composite of cardiovascular death, myocardial infarction, unplanned revascularization, ischemic stroke, and systematic thromboembolism during 12‐month follow‐up. The primary safety endpoint is major bleeding and clinically relevant nonmajor bleeding (CRNMB) defined by the International Society of Thrombosis and Hemostasis (ISTH) during 12‐month follow‐up.^20^ The composite secondary endpoint of net adverse events included all‐cause death (cardiovascular death, noncardiovascular death), acute myocardial infarction (fatal or nonfatal, Q‐wave or non‐Q‐wave), systemic thromboembolism, unplanned revascularization (target or nontarget vessel, target or nontarget lesion), stent thrombosis (possible, probable, definite), stroke (hemorrhage or ischemic) and bleeding (ISTH or Bleeding Academic Research Consortium [BARC] criteria) during 12‐month follow‐up.^20^, ^21^

Cardiovascular deaths include death from myocardial infarction, stroke, heart failure, aortic dissection, cardiac arrest (sudden death), cardiovascular operations, and unknown causes for which investigators fail to acquire any relevant information in the follow‐up.^21^ Myocardial infarction is defined in accordance with the fourth universal definition (types 1–5).^22^ Unplanned revascularization consists of unplanned PCI or surgical bypass for a >70% stenosis by coronary angiography with ischemic symptoms or a >90% stenosis with or without symptoms. Target vessel revascularization is defined as the revascularization of any segment of the target vessel. Target lesion revascularization is defined as revascularization for the target lesion or bypass surgery of the target vessel performed for restenosis or other complication of the target lesion. Stent thrombosis is defined referring to the criteria of the Academic Research Consortium.^23^ Stroke is defined as the presentation of acute vasogenic focal neurological defect with relevant symptoms and signs lasting ≥24 h, which should be confirmed by computed tomography or magnetic resonance imaging and categorized into a hemorrhagic stroke, ischemic stroke, subarachnoid hemorrhage, or undetermined stroke.^21^ Systemic thromboembolism is defined as an acute limb or organ (kidney, mesenteric artery, spleen, retina, or graft) vascular obstruction determined by imaging, surgery, or autopsy, with or without corresponding symptoms or signs.^23^ Bleeding is classified as (1) major bleeding, CRNMB, and minor bleeding by ISTH criteria; (2) types 1–5 with major bleeding ≥type 3a according to BARC criteria.^20^, ^21^ The detailed definitions of endpoints are summarized in Supporting Information: Appendix 4. All primary endpoints will be evaluated by an independent events review committee (ERC) blinded to treatment assignment.

